## Abstract

**Background:**

There is a high prevalence of pain and post-traumatic symptoms among refugees and feasible interventions to manage these are needed. However, knowledge about the effect of physiotherapy and psychological group interventions among refugees is scarce. Our aim is to determine whether two different interventions, the Physiotherapy Activity and Awareness Intervention (PAAI) and Teaching Recovery Techniques (TRT), reduce pain and post-traumatic symptoms among refugees from Syria living in Norway.

**Methods/design:**

Syrian adults with either pain disorders or post-traumatic symptoms, or both, will be recruited to this randomized control trial. The trial will include two separate interventions: participants with dominating pain symptoms will be assigned to the PAAI; and those with a predominance of post-traumatic symptoms will be assigned to the TRT intervention. Participants will be randomized to either the immediate intervention group or the delayed intervention group, for each of the interventions (PAAI and TRT). A minimum of 68 participants will be recruited for the PAAI and 78 participants for TRT, in order to detect clinically and statistically significant symptom improvement, assuming 25–30% attrition after recruitment. The main outcomes for the analyses will be pain intensity measured by the Brief Pain Inventory questionnaire and the scores of the Impact of Events Scale — Revised. The effect will be evaluated at the end of interventions lasting 8 weeks (PAAI) and 6 weeks (TRT) using the same instruments after the end of the intervention, and again 4–6 weeks later. Additionally, a qualitative evaluation will be conducted through an embedded process evaluation and personal interviews with participants after each of the interventions is finished.

**Discussion:**

Our study will determine the feasibility of the implementation of two different interventions and the effect of these interventions among refugees from Syria with pain disorders and/or post-traumatic symptoms.

**Trial registration:**

Clinical Trials.gov, NCT03951909. Retrospectively registered on 19 February 2019.

## Background and rationale

Both chronic pain and mental health symptoms can be a consequence of traumatic events [1, 2]. At the beginning of 2019, according to the United Nations High Commissioner for Refugees (UNHCR), 70.8 million displaced persons due to war and violent conflict were registered worldwide, of which 25.9 million were refugees. Syrians are one of the growing groups that have fled to Europe since the war began in 2011 [3, 4]. Norway is no exception, with more than 30,000 Syrian refugees living in the country by the end of 2018 [5–8]. Many refugees have been exposed to stressful events or situations that can lead to persistent distress [9]. As a consequence, the presence of pain disorders and mental health symptoms is common, both of them often in combination within the same individual [10, 11].

The complex relationship between torture, pain and other aspects of the individuals’ experience before and after migration has profound impacts on the everyday lives of many refugees [12]. Pain has been identified as a predictor of emotional distress among refugees [13], but there is a scarcity of population-based data about pain disorders among refugees from Syria. According to a Norwegian study, 76% of the traumatized refugees attending an outpatient clinic experienced chronic pain [14].

Mental problems of various types and degrees are prevalent among refugees, including Syrians. In Lebanon during 2011–2013, 44% and 61% of Syrian refugees reported depression, and some of them also loneliness, in two similar studies [15, 16]. In 2014, 54% of Syrians accessing International Medical Corps facilities in Syria and neighboring countries suffered severe emotional disorders, including depression and anxiety [9]. Among the Syrian refugees resettled in the USA, a high prevalence of post-traumatic stress disorders (PTSD) (32%), anxiety (40%) and depression (48%) has been reported [17].

Health care services for refugees during flight and in host countries shortly upon arrival are either non-existent, inadequate or insufficiently available, especially regarding chronic pain and mental health problems [18]. Inadequate health care for refugees can worsen their symptoms and lead to chronicity [10]. Once established in a host country, the national health services in most high-income countries are obliged to offer health care services to refugees. However, the lack of evidence regarding the best treatment choices for this population, together with limited resources, may compromise the health services provided to refugees. In addition, treatments are often only entitled to those with formally established diagnoses. However, many refugees who do not have enough symptoms for a formal PTSD or chronic pain diagnosis might still have symptoms like headaches or flash backs that go unmanaged and impede their learning of a new language and integration into society. It has been suggested that group treatment could be an approach to maximize the effect of the treatment for coping with symptoms among traumatized refugees, as well as a means to increase social interaction and well-being among participants [19].

The evidence on group-based physiotherapy for chronic pain among refugees is scarce. As far as we know, only a study in progress in Denmark has used mixed physical activity and basic body awareness therapy to reduce chronic pain for refugees with established PTSD [20]. A combination of psychomotor and general physiotherapy exercises is often used in Norway and other Nordic countries in group therapy, as this enables the health professional to recognize and normalize the participants’ emotions and movement patterns, capturing and preserving the individual treatment needs within the group, at the same time as having an overview of the social interactions [21]. However, the adequacy or effect of this therapy has not been well studied for refugees. The Physiotherapy Activity and Awareness Intervention (PAAI) package was adapted for this study based on this combination of psychomotor and general physiotherapy, and grounded on the extensive experience with immigrant patients of the physiotherapists in the team and according to users’ recommendations.

Teaching Recovery Techniques (TRT) is a self-help group intervention designed and evaluated for children by the Children and War Foundation for use on subjects exposed to war or natural disasters [22]. TRT is built to meet the needs of a large number of traumatized refugees who require interventions for mental support. It is based on the principles of cognitive behavioral therapy and on evidence-based methods for treating trauma. The intervention focuses on three main groups of symptoms following severe traumatization, namely invasive sensory impressions, bodily activation and avoidance. TRT has shown significant effect in terms of reducing the aforementioned symptoms among children surviving catastrophes and adolescent asylum seekers in Europe [23]. Among adolescents in Palestine, TRT significantly reduced post-traumatic stress symptoms and was evaluated as a cost-effective intervention [24]. However, the effect of TRT on adult refugees with post-traumatic symptoms has not been studied.

Taking the previous into consideration, there is a need to develop and evaluate techniques and methods to adequately deal with adult refugees with chronic pain and post-traumatic symptoms.

### Objectives

The main objective of this project is to evaluate the effect of two different interventions, separately, among adult Syrian refugees with pain and/or post-traumatic symptoms:
The Physiotherapy Activity and Awareness Intervention (PAAI) in reducing the degree of pain, and secondarily in reducing post-traumatic symptoms (if present)The Teaching Recovery Technique (TRT) group intervention in reducing the degree of post-traumatic symptoms, and secondarily in reducing the degree of pain (if present)

## Methods

### Study design

This is a 2 × 2 armed randomized control trial (RCT) to study the effect of two different interventions for treating pain and post-traumatic symptoms (Fig. 1). Participants with dominating pain symptoms will be assigned to the PAAI and those with a predominance of post-traumatic symptoms will be assigned to the TRT intervention. Participants within each of the arms are randomized to either the immediate intervention group or the delayed intervention group, which will receive the same intervention but at a later time point. The study protocol follows the SPIRIT recommendations for intervention trials (Fig. 2, Additional file 5).

**Fig. 1 Fig1:**
[figure not shown]
Flowchart overview of the interventions. PAAI Physiotherapy Activity and Awareness Intervention, Q0 Questionnaire 0, Q1 Questionnaire 1, TRT Teaching Recovery Techniques

**Fig. 2 Fig2:**
[figure not shown]
Standard Protocol Items: Recommendations for Interventional Trials (SPIRIT) schedule of enrolment, interventions and assessments. PAAI Physiotherapy Activity and Awareness Intervention, Q0 Questionnaire 0, Q1 Questionnaire 1, TD delayed intervention (same intervention at a later time point), TRT Teaching Recovery Techniques

In addition, to examine the process of how the interventions improve health, a qualitative embedded process evaluation using personal observation of the intervention groups and individual semi-structured interviews will be conducted to gain an in-depth understanding of the mechanisms of action and key contextual variables affecting the intervention.

### Study setting

People suffering from chronic pain in Norway are generally followed up by primary health care including general practitioners and physiotherapists. However, in many regions including Bergen there is limited availability of treatment and follow-up, especially when an interpreter is needed. Similarly, people suffering from mental health suffering are generally followed up by primary health care and/or tertiary health care including general practitioners and psychologists (generally with need for referral). However, in many regions including Bergen there is limited availability of follow-up by psychologists, and specific cultural competence is scarce.

### Participants and recruitment

We recruit adult Syrian refugees (age ≥ 16 years) living in Bergen and adjacent municipalities from several arenas: educational activities in which the newly arrived immigrants initially are enrolled in groups of approximately 30 students; patients from health care providers both in primary and secondary care and pharmacies, especially from areas with a high number of immigrants; and other non-health related locations where refugees often gather, like specific immigrant shops (e.g. Middle-Eastern and Asian grocery stores). In these settings, adults from Syria are shortly informed about the study in Arabic by the first author, who speaks Arabic and Norwegian. Adults with either pain or post-traumatic symptoms who are willing to participate are given an individual appointment for further information and potential inclusion. At this point, those consenting fill out the baseline questionnaire (Q0 — see Additional file 1). This questionnaire is used to identify participants fulfilling the inclusion criteria regarding pain and/or post-traumatic symptoms. All participants are invited to contact the first author for more information at any point of the study.

### Inclusion criteria

Participants have to report either pain or post-traumatic symptoms in order to be included in one of the two interventions. Patients with physical pain are included if they report chronic pain that has lasted more than 6 months and score 3 or higher for either of the two items about pain severity on the Brief Pain Inventory (BPI) short questionnaire assessing average and current pain ranging from 0 to 10 [25]. Patients who answer yes to the question “Have you experienced any of these or some other terrifying event(s)?” and score over 24 on the revised Impact of Events Scale (R-IES) are included. The IES-R yields a total score ranging from 0 to 88 [26]. Patients scoring 20 or more on the General Health Questionnaire-12 (GHQ-12) are referred to a consultation with one of our collaborating psychologists in Bergen municipality before invitation to group participation, to make sure that he or she can benefit from group participation. If group participation is considered unfitting, the patient is referred to individual treatment.

Participants are allocated to either the PAAI or the TRT intervention according to their symptoms. Participants who present both pain complaints and post-traumatic symptoms in whom symptom scores measured as a relative percentage of the maximum respective scales, BPI and IES-R, are highest are invited to the intervention treatment.

### Exclusion criteria

Potential participants are excluded if they report health conditions requiring close medical follow-up, like diabetes with complications or cancer under treatment, or score on the mental health questions as having a serious mental illness (25 or more on the GHQ-12) and are assessed by psychologists to need individualized therapy. These patients will be referred to the appropriate level of care. Practical situations that impede attendance to treatment on a regular basis, like living far away from the therapy locations, are also a reason for exclusion.

### Allocation and blinding

A random allocation sequence was generated by a statistician using the ralloc command in Stata version 15. The sequence was obtained using a 1:1 allocation ratio in block randomization with block sizes varying between 4, 6 and 8. Separate randomization sequences were made for the PAAI and TRT. After generation of the lists, each line was numbered from 1 upward, reflecting the order of recruitment (participation number). Participants were individually randomized. To be able to recruit within periods that are shorter than the time delay between intervention and delayed list groups (6–8 weeks), and in order to be able to provide interventions of adequate size, recruitment is organized in three waves followed by three rounds of interventions.

It will not be possible to blind the participants or the instructors in this study during the active intervention phase. The person who recruits participants and assigns participation numbers does not have access to the randomization list. Unfortunately, this person (WH) is both recruiting and assessing outcomes and we only have one statistician, so further blinding is not possible.

### Interventions

In collaboration with Bergen municipality, the Centre for Crisis Psychology and the users, two interventions were developed and adapted to our population.

#### Physiotherapy Activity and Awareness Intervention (PAAI)

The physiotherapy treatment is based on principles from Norwegian psychomotor physiotherapy and general physiotherapy exercises and is led by physiotherapists working at Bergen municipality. In order to ensure the follow-up and guiding of each person, and to be able to handle reactions that might occur, 10–12 persons are invited into each group. Interpreters are oriented on their role in the group as well as the exercises. The words and phrases the therapists will use for instruction are shared with the interpreters beforehand, as there might be variants of Arabic depending on the country background of the interpreters. The intervention consists of eight sessions lasting approximately 1 h each with the same key elements each time: an introduction with welcome ball game and mindfulness exercises; sitting on the chair with a number of movements; lying down and relaxation; standing proprioceptive exercise; active movements stimulating balance, coordination and breathing; and, finally, grounding and short closing round.

The instructors explain the therapy and advise the participants to pay attention to their own limitations, for example, regarding pain and range of motion. Each participant is encouraged to do as much as possible of the exercises, within her or his capability at the beginning of each session. Otherwise, any injuries will be reported in the study and followed by the physiotherapists within the regular health care system.

#### Teaching Recovery Techniques (TRT)

TRT is designed in a step-by-step practical way to develop skills and techniques helpful in coping with the psychological effects of serious traumatization. In our case, the manual is adjusted for adults, with relevant examples and homework. All health professionals and collaborating interpreters involved in this intervention have previously been trained on the TRT manual by the Centre for Crisis Intervention. TRT is scheduled to one session weekly for 6 weeks; one session lasts approximately 2.5 h with up to 15 participants. The sessions deal with intrusive thoughts and feelings, arousal and avoidance in this order. To avoid secondary exposure and traumatization, participants are not required to disclose examples from their own life during group meetings, but they are asked to bring back memories of what happened to them. Participants will have tasks that are considered safe to carry out as homework.

### User involvement in development of the interventions

Representatives from the Syrian population in Bergen participated in a consulting group and contributed to the development of the interventions in May–June 2018. Eight persons from Syria, including both women and men, with different backgrounds and positions in society, were recruited and asked for their general opinion of the interventions regarding various subjects. These included: the need for gender-segregated or age-segregated groups; the frequency, the most appropriate time of the day and day of the week to conduct group sessions; the importance of socializing; the need to coordinate childcare during the sessions; the necessity of reminders (by SMS) prior to each session; giving recommendations on appropriate clothing for the sessions; preferences for interpreters; and so on. We will try to follow this advice as much as possible, including separate groups for women and men, in the implementation of the interventions.

### Sample size calculation

For calculation of statistical power, we assumed that differences at baseline will be random for the immediate intervention and delayed intervention groups. We calculated the necessary sample size using an independent-sample *t* test with 80% power and a significance level of 5%. We used mean and standard deviation values based on earlier findings by our research group among 150 refugees from Syria in Lebanon waiting to be sent to Norway (not yet published).

For the PAAI, we assumed a mean of 6.0 and SD of 3.8 in the BPI “normal” pain scale (range 0–10) and considered as clinically significant a difference of 3 points on the given scale. These calculations gave a minimum size of 27 participants in each of the immediate and delayed PAAI groups. Assuming 25% attrition, the numbers needed are 34 participants in each of the study arms; this is to say, a total of 68 participants are needed for the PAAI. Since each PAAI group will have approximately 10–12 participants, we will need 3–4 immediate intervention groups and 3–4 delayed intervention groups for the PAAI. Similarly, for the TRT intervention we assumed a mean of 35.6 points and SD of 15, 5 on the IES-R scale (range 0–80) and 13.1 points in change as clinically significant (and SD of 0.75). These calculations gave a study size of 30 participants for the immediate and delayed TRT groups. We allowed a 30% dropout for this type of intervention, giving 39 participants per study arm. Thus, 78 participants are needed for TRT. Since each group will have approximately 10–12 participants, we will need 3–4 immediate intervention groups and a similar number of delayed intervention groups for the TRT intervention.

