### Analysis and statistical methods

Baseline characteristics will be presented separately for the two groups within each of the two trial arms (PAAI and TRT), with medians and interquartile range for continuous variables and counts and percentages for categorical variables. All data will be analyzed according to the intention-to-treat principle. All tests will be two-sided and 5% will be used as the level of significance. The trial will follow the CONSORT guidelines for publication of results.

The immediate effect of the interventions will be assessed by comparing the scores of the immediate intervention participants at the last treatment session (6 or 8 weeks for TRT and the PAAI, respectively) with the scores of the delayed intervention participants right after they begin their intervention. This will mean a 1-week delay in the measurements of both groups. The effect after 6/8 weeks will be assessed using linear regression, with the continuous measure of the outcome at 6/8 weeks (BPI, IESR) as the dependent variable and the allocation group as the independent variable with adjustment for baseline score of the outcome. The effect will be reported as regression coefficients with 95% confidence intervals and can be interpreted as the mean difference in scores after 6/8 weeks between the immediate intervention and the delayed intervention groups after adjustment for potential differences in outcome at baseline. Because group dynamics and other aspects of group membership could cause correlations between individuals within groups, we will calculate intraclass correlation coefficients for the outcomes and apply mixed-effects linear regression with random intercept and slope for group membership. Missing data will be considered, and appropriate multiple imputations based on characteristics measured at baseline will be done when necessary. As all participants will receive the intervention, additional cohort analyses will be conducted to supplement evaluation of the duration of the effect of the interventions.

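### Both sample sizes are inflated for attrition by multiplying by 1.25 and 1.30, so 68 and 78 fall slightly short of the plan's own 27 and 30 evaluable per arm

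*Protocol article*

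**What the plan says.** The sample size section of the protocol article bases both trials on an independent-sample t test with "80% power and a significance level of 5" per cent. For PAAI, "we assumed a mean of 6.0 and SD of 3.8 in the BPI" item for usual pain, and the authors "considered as clinically significant a difference of 3 points on the given scale". This yields at least 27 per arm. The allowance for loss follows: "Assuming 25% attrition, the numbers needed are 34 participants in each of the study arms", or 68 in total.

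For TRT, the section gives a mean of 35.6 on the IES-R, an SD printed with a broken decimal (read here as 15.5), a change of 13.1 points as clinically significant, and in brackets a further SD of 0.75 that is not explained. It arrives at 30 per arm and continues: "We allowed a 30% dropout for this type of intervention, giving 39 participants per study arm", or 78 in total.

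The abstract carries the totals forward: "A minimum of 68 participants will be recruited for the PAAI and 78 participants for TRT". It describes the 25–30% as attrition occurring after recruitment.

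**The concern.** If a fraction d of those recruited is lost, recruiting N per arm leaves N(1 − d). To finish with n evaluable, N must be n/(1 − d). Multiplying n by (1 + d) always gives a smaller number, and the gap widens as d grows. The protocol prints the required number, the loss rate and the result for each intervention, and the three do not agree in either case.

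What is at stake is whether the recruitment minimum still supports the planned power at the loss the authors expected. The Discussion relies on the study size being sufficient for the primary objectives.

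**Working it through.** **Inputs**
- Test and error rates: independent-sample t test, 80% power, 5% level (sample size section); two-sided ("All tests will be two-sided and 5% will be used as the level of significance", analysis section); equal arms ("The sequence was obtained using a 1:1 allocation ratio in block randomization", allocation section).
- PAAI: difference 3, SD 3.8, required 27 per arm, attrition 25%, stated 34 per arm.
- TRT: difference 13.1, SD 15.5 (assumed reading), bracketed 0.75 (meaning unclear), required 30 per arm, dropout 30%, stated 39 per arm.
- Base of the loss rate: those recruited (abstract).

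**1. Reproducing the base numbers** (exact two-sample t test, two-sided 5%, 80% power)
- PAAI: 3/3.8 = 0.789, which needs 26.2, so 27 per arm. The plan's 27 reproduces.
- TRT on 13.1 points and SD 15.5: 13.1/15.5 = 0.845, which needs 23 per arm, not 30.
- TRT with 0.75 taken as a standardised effect: needs 28.9, so 29 per arm, close to 30.

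**2. Reproducing the inflated numbers**
- n × (1 + d): 27 × 1.25 = 33.75, rounded up to 34; 30 × 1.30 = 39. Both stated figures match.
- n/(1 − d): 27/0.75 = 36; 30/0.70 = 42.9, rounded up to 43. Neither stated figure matches.

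**3. What the stated sizes leave**

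| | PAAI | TRT |
|---|---|---|
| Stated per arm (total) | 34 (68) | 39 (78) |
| Left at the planned loss | 34 × 0.75 = 25.5 | 39 × 0.70 = 27.3 |
| Required | 27 | 30 |
| Shortfall per arm | 1.5 | 2.7 |
| Largest loss that keeps the required number | 1 − 27/34 = 20.6% | 1 − 30/39 = 23.1% |
| n/(1 − d) per arm (total) | 36 (72) | 43 (86) |
| Difference in total | 72 − 68 = 4 | 86 − 78 = 8 |

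**4. Power at what is left** (noncentral t, two-sided 5%)

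| Scenario | At the required n | At the planned loss |
|---|---|---|
| PAAI, 3 points, SD 3.8 | 81.2% (27) | 78.9% (25.5); 78.1% at 25, 79.7% at 26 |
| TRT, standardised effect 0.75 (assumption) | 81.5% (30) | 77.6% (27.3) |
| TRT, 13.1 points, SD 15.5 | 89.6% (30) | 86.5% (27.3) |

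**The case against.** **The effect is small.** This stands. For PAAI the exact requirement for 80% power is 26.2 per arm, so 25.5 is only about 0.7 of a participant short of it. Power falls by 2.3 points from its value at 27 (81.2% to 78.9%).

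**The analysis is not the unadjusted t test.** The analysis section plans linear regression adjusted for the baseline score, which usually gains precision. The documents give no baseline-to-follow-up correlation r, so any figure is an assumption. Scaling the variance by (1 − r²), PAAI power at 25.5 per arm would be about 80.5% at r = 0.2, 82.6% at r = 0.3 and 89% at r = 0.5. Against that, the same section expects correlation within treatment groups, which works the other way and for which the sizing makes no allowance. Neither effect enters the stated calculation, so neither corrects it. Together they do show that the attrition formula is unlikely to decide this trial's power.

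**Imputation keeps everyone in the analysis.** The plan provides for intention-to-treat analysis, with multiple imputation from baseline characteristics when necessary. But the sample size section itself counts those lost as lost, and imputing from baseline data does not restore unobserved outcomes.

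**The loss rate might be a share of the required number.** On that reading, multiplying would be right. The abstract excludes it by placing the attrition after recruitment.

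**The totals are minimums.** This also stands. The text does not cap recruitment at 68 and 78, and the number actually enrolled is not reported, so a shortfall in the completed trial cannot be shown.

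**A stronger reading to avoid.** A reader might infer that both trials fall below 80% power. For TRT the documents do not support this. It needs the unexplained 0.75 to be a standardised effect, which the text does not say and which gives 29 rather than 30. On 13.1 points and SD 15.5, power stays at about 87%, because those inputs need only 23 per arm.

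**Conclusion.** The inflation step is wrong for both interventions. At the plan's own loss rates, 68 and 78 leave 25.5 and 27.3 per arm against the required 27 and 30; they cover about 21% and 23% attrition, not 25% and 30%. This follows from the printed figures and from the abstract's statement that the rate applies after recruitment.

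For PAAI, the promised 80% power is narrowly missed, at about 79% under the plan's own t test. For TRT, only the shortfall against the stated 30 is established. Power at 27.3 per arm is about 78% or about 87%, depending on which printed figure defines the effect, and 15.5 is itself a reading of a broken number. How the TRT base of 30 was obtained is a separate question.

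The severity is minor: no allocation, outcome or analysis depends on it.

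**What to change.** Enrolment was completed in September 2019 according to the trial status section, so replacing the targets with 72 and 86 would rewrite them after the fact. It would also give weight to a TRT base of 30 that does not follow from 13.1 points and SD 15.5. Instead:

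- In the sample size section and the abstract, state that 68 and 78 cover about 21% and 23% attrition for the required 27 and 30 per arm.
- Report the power at the planned 25% and 30% loss: about 79% for PAAI at 25.5 per arm. For TRT at 27.3 per arm, say which difference and SD (or standardised effect) is assumed and give the matching power: about 78% at 0.75, about 87% at 13.1 points and SD 15.5.

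The cost is wording only. The stated figures become slightly less favourable.

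### The TRT sample size of 30 per arm cannot be reproduced from its stated inputs, and the undefined figure of 0.75 leaves the planned difference unclear

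*Protocol article*

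**What the plan says.** All of the sizing is in the Sample size calculation section of the protocol article. Both trials were sized "using an independent-sample *t* test with 80% power and a significance level of 5" percent. For TRT, "we assumed a mean of 35.6 points and SD of 15, 5 on the IES-R scale (range 0–80" is followed by "13.1 points in change as clinically significant (and SD of 0.75" in brackets. The result is given as "These calculations gave a study size of 30 participants for the immediate and delayed TRT groups". An allowance of 30% for dropout then takes this to 39 per arm and 78 in total.

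Two other sections complete the specification. Under Analysis and statistical methods: "All tests will be two-sided and 5% will be used as the level of significance" percent threshold. Under Allocation and blinding: "The sequence was obtained using a 1:1 allocation ratio in block randomization".

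On the scale itself, the sizing section gives a range of 0–80, whereas the Inclusion criteria section says "The IES-R yields a total score ranging from 0 to 88", and the Outcomes section also gives 0 to 88.

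**The concern.** A t-test sample size for a difference in means needs one difference and one SD. The TRT paragraph prints one difference (13.1) and two quantities called an SD (15, 5 and 0.75). The second cannot be an SD on the same scale as the first. If it is a standardised effect with the wrong label, it disagrees with the ratio of the other two figures, 13.1/15.5 = 0.845.

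The planned difference is therefore at stake. A reader who later meets a null or borderline TRT result will want to know whether the trial was designed to detect 13.1 points or something nearer 11.6, and with what power. The paragraph does not settle this.

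**Working it through.** **Inputs.** Independent-sample t test, 80% power and 5% level (Sample size calculation); two-sided (Analysis and statistical methods); 1:1 allocation (Allocation and blinding); TRT difference 13.1, SD 15.5 (from the printed 15, 5), the figure 0.75, 30 per arm and 30% dropout (Sample size calculation).

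**Formula.** With d = difference/SD, the normal approximation is n per arm = 2(1.960 + 0.842)²/d² ≈ 15.70/d². The t test, solved with the noncentral t distribution, adds about one participant per arm. The t-test result is used below because that is the stated method.

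**Check of the method on the PAAI figure.** d = 3/3.8 = 0.789. The t test gives 26.2, so 27 per arm, which is the figure printed for PAAI. The method is therefore the one the authors used, and a difference of software or formula does not explain the TRT result.

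**TRT as printed.** d = 13.1/15.5 = 0.845. Normal approximation: 15.70/0.714 = 22.0. The t test gives 22.98, so **23 per arm** against 30 stated. Power at 30 per arm is 89.6%. Reading the SD as 15 gives 22 per arm.

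**TRT with 0.75 taken literally as the SD.** d = 13.1/0.75 = 17.5, and the formula returns 1 per arm. This reading is untenable.

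**TRT with 0.75 taken as a standardised effect.** Normal approximation: 15.70/0.5625 = 27.9. The t test gives 28.9, so **29 per arm**; power at 30 is 81.5%. This conflicts with the printed inputs in one of two ways: either the difference is 0.75 × 15.5 = 11.6 points, or the SD is 13.1/0.75 = 17.5.

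**Other readings tried.**

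| Reading | n per arm |
|---|---|
| 13.1/15.5, one-sided 5%, 80% power | 19 |
| 13.1/15.5, two-sided, 90% power | 31 (30 by normal approximation) |
| 0.75 as a baseline–follow-up correlation, SD 15.5 | 10–11 (normal approximation) |
| 23 already inflated by 1.3 | 29.9 |
| 13.1 with SD 17.5 (d = 0.749) | 29.006, so 30 |

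The rows that come near 30 each need something the article does not state: 90% power, dropout applied twice, or an SD of 17.5. Working backwards, exactly 80% power at 30 per arm needs d = 0.736, that is, an SD of 17.8 for 13.1 points or a difference of 11.4 points for SD 15.5.

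**After dropout.** 39 = 30 × 1.3. If 30% are lost, 39 × 0.70 = 27.3, so about 27 per arm are evaluable. Power at 27 is 86.2% if d = 0.845 and 77.2% if d = 0.75.

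**The case against.** The best defence is that the paragraph contains a labelling slip and the design is sound. If 0.75 is the standardised effect, the t test needs 29, and 30 is one more than that. If the SD was really 17.5, then 13.1/17.5 rounds to 0.75 and the calculation rounds up to exactly 30, so a single misprint would explain everything. Under the figures as printed, 30 is more than enough. The sizing inputs do not enter the planned regression or mixed model, and the Trial status section says enrolment was completed in September 2019.

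Most of this stands. A reader might infer from the faulty inputs that the TRT trial is underpowered, or that its 80% power has no support. The documents do not bear that out: at 30 evaluable per arm both workable readings give at least 80%. A reader might also infer that the 0–80 range damages the calculation. It does not, because the range is not an input to a t-test sample size.

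The defence does not restore traceability. The article prints 15, 5 and not 17.5, calls 0.75 an SD, and says nothing that lets a reader choose between the explanations. Nor is this detail that an article would leave to a fuller document: the article prints the calculation, and its parts disagree.

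**Conclusion.** The stated 30 per arm is not reproducible from its stated inputs, and 0.75 is undefined. The printed difference and SD need 23 per arm, 7 fewer than stated. The most natural repair needs 29, at the price of a difference or SD that the article does not give. The consequence is uncertainty about the planned difference (about 11.6 or 13.1 points) and about the design power (81.5% or 89.6% at 30 evaluable), not a demonstrated shortfall.

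Power falls below 80% in one conditional case: the effect is 0.75 SD and the full 30% are lost from 39 per arm, which leaves about 77%. That comes from multiplying by 1.3; dividing by 0.70 would have given 43 per arm. It is a reason to state the power after loss, and it does not show that the trial missed its target.

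The result assumes that 15, 5 means 15.5; SD 15 leaves the conclusion unchanged. All power figures are for the unadjusted, individually randomised t test that the section specifies. Baseline adjustment and correlation within treatment groups would alter them, but the article gives no values for either.

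**What to change.** In the Sample size calculation section:

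- State what 0.75 is. Only the authors know, so it should be defined before anything is deleted or replaced.
- Give one consistent set of difference, SD and power. With 13.1 points and SD 15.5, this is 23 per arm at 80% power, or 30 per arm at 89.6%. With a standardised effect of 0.75, give the difference and SD that produce it (about 11.6 points with SD 15.5, or 13.1 points with SD about 17.5); this is 29 per arm at 80%, or 30 at 81.5%.
- Restate the power for 39 per arm after 30% loss, that is, with about 27 evaluable: about 86% under the first set and about 77% under the second.
- As a side correction with no effect on the sample size, change the IES-R range from 0–80 to 0–88 to agree with the Inclusion criteria and Outcomes sections.

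The cost is one recalculation and a few words. Neither enrolment nor the planned analysis changes.
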